### Study assessments

The schedule of study outcome assessments is outlined in Fig. 2. Study assessments will be scheduled upfront and participants will be regularly reminded (by email and phone) to ensure complete follow up. Primary, secondary, and exploratory outcomes will be measured in all participants at three different time points:t_0_ (baseline assessments): between 0 and 14 days prior to the first chemotherapy sessiont_2_ (post-treatment assessments): between 1 and 5 days after the end of AC-CTt_3_ (follow-up assessments): after 3 months of t_2_

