**Fig. 2 Fig2:**
[figure not shown]
The schedule of enrolment, interventions, and assessments. -t_0_, enrolment process; t_0_, baseline; t_1_, during anthracycline-containing chemotherapy; t_2_. post anthracycline-containing chemotherapy (which coincides with the end of the intervention); t_3_, 3 months after t_2_; NT-proBNP, N-Terminal pro-brain natriuretic peptide; LV, left ventricular

In addition, for analysis of circulating NT-proBNP, blood samples will be collected between 1 and 24 h before each AC-CT cycle (t_1_: during treatment assessments). Patients will be instructed and reminded to avoid drinking beverages containing alcoholic or caffeine, and to abstain from smoking for 12 h prior to, and avoid vigorous physical activities for 24 h prior to all examinations.

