### Statistical analyses

Statistical data analysis will be performed using the Statistical Package for the Social Sciences. The statistical significance will be set at a *p* value <0.05. Intention-to-treat and per-protocol approaches will be used both for all analyses. Data analysis will start with standard descriptive methods to describe the data (means and standard deviations will be calculated for continuous variables and absolute and relative frequencies for categorical variables).

Continuous variables will be compared between the two study groups using one-way analysis of covariance (ANCOVA), adjusted for the effect of the baseline values (covariate). A linear two-way mixed ANCOVA model with repeated measures (t1, t2 and t3) will be performed to test the difference over time between the two study groups and interaction (Group × Time), on primary and secondary outcomes, with the same covariate as the one-way ANCOVA. Bonferroni’s post-hoc procedure will be performed to locate the pairwise differences. Normality will be verified by the Kolmogorov-Smirnov test and the homogeneity of the variance will be validated by Levene’s test. Effect size will be calculated to estimate variance between moments through partial eta-squared. The cutoff values were defined as 0.02 for small effect size, 0.13 for moderate, and 0.26 for large effect sizes [36]. The chi-squared test will be used to check for a relationship between categorical variables. The effect size will be calculated using Cramer’s V test and interpreted based on the following cutoff values: 0.10 for a small effect, 0.30 for a medium effect, and 0.50 for a large effect. [36] No interim analyses will be conducted.

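### If the repeated-measures ANCOVA is run with baseline as measured, the Time test and its partial eta-squared refer to a baseline of zero; centring baseline would remove this minor fault at no cost

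*Protocol article*

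**What the plan says.** All of this is in the Statistical analyses section of the protocol article, unless another section is named.

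- Software: "Statistical data analysis will be performed using the Statistical Package for the Social Sciences".
- Covariate of the one-way ANCOVA: the comparison is "adjusted for the effect of the baseline values (covariate").
- Longitudinal model: "A linear two-way mixed ANCOVA model with repeated measures (t1, t2 and t3").
- Stated purpose of that model: "to test the difference over time between the two study groups and interaction (Group × Time").
- Scope and covariate of that model: the article applies it "on primary and secondary outcomes, with the same covariate as the one-way ANCOVA".
- Effect size: "Effect size will be calculated to estimate variance between moments through partial eta-squared". It is graded at 0.02, 0.13 and 0.26 (small, moderate, large).
- Pairwise differences are located with a Bonferroni post-hoc procedure, and Levene's test is used for homogeneity of variance.

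The Study assessments section says: "Primary, secondary, and exploratory outcomes will be measured in all participants at three different time points". These are t0, t2 and t3. The t1 samples serve NT-proBNP only ("blood samples will be collected between 1 and 24 h before each AC-CT cycle"). LVEF and strain therefore have two post-baseline values, t2 and t3.

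The text does not say whether baseline is raw or centred, whether a baseline × Time term is in the model, or which SPSS procedure is used.

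**The concern.** A mixed ANCOVA with Levene's test, Bonferroni comparisons and partial eta-squared, run in SPSS, reads most naturally as the repeated-measures GLM. I take it that this procedure crosses every between-subject term, covariates included, with the within-subject factor. That is software behaviour, not something the article states.

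Once baseline × Time is in the model, the Time main effect is the change between visits where the covariate equals zero. If baseline is entered as measured, that means an LVEF of 0% or a strain of 0. The intended null is no average change between visits. The null tested would be no change in a patient who cannot exist, and the result would depend mainly on whether the baseline slope differs between visits.

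At stake is the partial eta-squared for variance between time points, most naturally the effect size of Time. It could be graded below small when the change is large, or a Time effect could be declared when there is none. The Bonferroni comparisons of adjusted means, if taken at the mean baseline, would be right and could contradict the omnibus Time test beside them.

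**Working it through.** **Inputs from the article.** The plan gives no figure for the Time effect, so there is none to reproduce. The evaluable number is 72, from Sample size calculation: 90 × (1 − 0.20) = 72. LVEF and strain have two post-baseline visits.

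**Assumed inputs (the article gives none).** LVEF mean m = 62 and SD = 5; correlation between t2 and t3 of 0.7; baseline correlations with t2 and t3 as stated per case; equal SD at all visits, so each correlation is also a slope; two-sided 0.05.

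**Formula.** With two visits, the Time test is the intercept of D = Y(t3) − Y(t2) regressed on group (coded −0.5/+0.5) and baseline, with 72 − 3 = 69 residual degrees of freedom. Let s be the residual SD of D.

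- Centred baseline: SE = s × √(1/n).
- Raw baseline: SE = s × √(1/n + m²/((n − 1)SD²)), and the estimate moves by −(difference in slopes) × m.
- Partial eta-squared = t²/(t² + 69).

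The multipliers are √(1/72) = 0.118 for centred and √(1/72 + 62²/(71 × 25)) = √(0.0139 + 2.1656) = 1.476 for raw. The raw-baseline standard error is 1.476/0.118 ≈ 12.5 times as large, because zero lies 62/5 = 12.4 SDs below the mean.

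**Case 1: true 0.5-SD change, correlations 0.6 and 0.6.** s² = 2 × 25 × (1 − 0.7) = 15, so s = 3.873. The change is 0.5 × 5 = 2.5.

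- Centred: SE = 0.456, expected t = 5.48, rejection 100%, partial eta-squared = 30.0/(30.0 + 69) = 0.30.
- Raw: SE = 5.718, expected t = 0.44, rejection 7%. The simulated median partial eta-squared is 0.008.

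**Case 2: no true change, correlations 0.7 and 0.5.** The slope difference is −0.2, so s² = 15 − 0.04 × 25 = 14 and s = 3.742.

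- Centred: the estimate is centred on 0, and rejection is at the nominal 5% (5 to 6% in simulation).
- Raw: the intercept is 0.2 × 62 = 12.4, SE = 5.524, expected t = 2.24, rejection 60%.

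**Variations.**

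| Assumption | Raw | Centred |
|---|---|---|
| LVEF, true 0.3-SD change, correlations 0.6/0.6 | 6% | 90% |
| LVEF, no change, correlations 0.7/0.6 | 19% | 5% |
| Strain (assumed magnitude 20, SD 2.5), true 0.5-SD change, correlations 0.6/0.6 | 10% | 100% |
| Strain, no change, correlations 0.7/0.5 | 60% | 5% |

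Simulated trials agree with these figures to within one or two percentage points (median partial eta-squared 0.31 centred in Case 1).

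**A separate simulation with a different error structure.** It used n = 72, LVEF 62 and SD 5, and a true 3-point fall between visits with equal slopes. The median partial eta-squared was 0.008 raw, 0.376 centred, and 0.373 raw without a baseline × Time term. With no change and slopes of 0.6 and 0.4, rejection was 54% raw against 5.6% centred. With three post-baseline time points and a true change, partial eta-squared was 0.014 raw against 0.462 centred.

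**What does not move.** The Group and Group × Time F values were the same under both codings (largest difference about 1e-12). Centring changes only where the Time effect is evaluated.

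**The case against.** The strongest objection is that the fault is not in the text. The article does not say that baseline is raw, that baseline × Time is fitted, or that the GLM procedure is used. A linear mixed-model procedure, in which the analyst chooses the terms, would also fit the description. Without the baseline × Time term, or with a centred baseline, the problem disappears. Covariate coding is also commonly left to an analysis plan, and none is shown. This stands, and makes the point conditional. It does not remove it, because the article itself fixes the covariate, the effect-size statistic, what that statistic is to measure and its cut-offs, and the most natural way of running that combination does not deliver the stated quantity.

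The second objection is that Time is not a stated hypothesis. The model's named targets are the group difference over time and Group × Time, and visit differences are located by the post-hoc comparisons. This also stands. Time enters mainly through the effect size, and even there the wording is loose enough that partial eta-squared might be reported for the unaffected terms.

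A reader might infer that the planned effect size is simply wrong, that the trial's primary conclusion is at risk, or that recovery between t2 and t3 will be judged from the Time test. The documents support none of these. The coding is unstated, the between-arm tests are identical under both codings, and no passage assigns the question of recovery to the Time test. Nor does any passage say that baseline correlation falls over time; that is an assumption of the second case.

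**Conclusion.** The point holds as a conditional and minor one. If the model is run as the repeated-measures GLM with baseline as measured, the Time test and its partial eta-squared can be badly off in either direction for outcomes whose values lie many SDs from zero. For LVEF, a true 0.5-SD change would be found about 7% of the time instead of 100%, with a large effect (0.31) graded below small (about 0.01). With no true change, rejection could reach about 60% instead of about 6%.

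These sizes rest on the assumed means, SDs and correlations and on the assumed software behaviour. With slopes that differ less, the false-rejection figure drops to about 19%. NT-proBNP was not examined, because the article gives nothing on its distribution and zero may lie nearer its data.

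Group, Group × Time and pairwise comparisons at the mean baseline are unaffected, so the between-arm conclusion and the sample size stand.

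**What to change.** In the Statistical analyses section, state that in the repeated-measures model each outcome's baseline value enters centred at its grand mean over the analysed patients, and that the Time test and the partial eta-squared between time points are taken from that model.

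The cost is one sentence and one computed variable per outcome. It needs no further data or patients, and the Group and Group × Time results stay the same.

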### Self-reported physical activity level

The International Physical Activity Questionnaire-Short (IPAQ-SF) will be used to calculate the metabolic equivalent (MET) minutes per week spent in walking and in moderate and vigorous activities. Sedentary behavior will be determined based on time spent sitting per day (minutes). Based on their scores, participants will be categorized as having a low, moderate, or high physical-activity level. The Portuguese language version of the IPAQ-SF will be used [33]. Scoring will be analyzed by the first author (PA), not blinded to the patient assignment group.

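### If the chi-squared test is the between-arm test of the three-level activity class, it ignores both the order of the levels and the baseline class; the test is valid but less efficient, and the outcome is secondary

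*Protocol article*

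**What the plan says.** The Statistical analyses section sets two routes.

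- Continuous variables are compared between arms "using one-way analysis of covariance (ANCOVA), adjusted for the effect of the baseline values (covariate"). A repeated-measures mixed ANCOVA with the same covariate follows, on primary and secondary outcomes.
- For categorical variables: "The chi-squared test will be used to check for a relationship between categorical variables". Then: "The effect size will be calculated using Cramer’s V test", with cutoffs for small, medium and large effects. No other categorical method is given.

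The section on self-reported physical activity produces both kinds of variable from one questionnaire. It "will be used to calculate the metabolic equivalent (MET) minutes per week spent in walking and in moderate and vigorous activities", and it also yields daily sitting time in minutes. After that, "Based on their scores, participants will be categorized as having a low, moderate, or high physical-activity level". This class is the only categorical variable among the listed primary and secondary outcomes.

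Under Study assessments, "Primary, secondary, and exploratory outcomes will be measured in all participants at three different time points", namely t0, t2 and t3, so a baseline class is planned for every participant. The Hypothesis section treats physical activity as exploratory and expects it to increase with exercise; the outcome list places it among the secondary outcomes.

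**The concern.** Low, moderate and high are ordered, and the expected effect has a direction. A Pearson chi-squared test on a table of two arms by three classes spends 2 degrees of freedom on any difference in pattern and gives the same result however the three columns are arranged. It has no place for the t0 class, although the plan uses the baseline value for every continuous outcome. Cramer's V is computed from the same statistic and has no sign.

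At stake is the chance of detecting a real upward shift in the activity class, and a reported effect size that cannot by itself show whether exercise raised or lowered activity.

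**Working it through.** **1. Sample size used.** The article gives no power for the activity class. Its sizing is for LVEF: effect size 0.6, 80% power, level 0.05, 72 evaluable, and 72/(1 − 0.20) = 90 randomized. A two-sample t test with d = 0.6 needs 35.04, so 36 per arm (72 in total), at one-sided 0.05; two-sided it needs 44.6, so 45 per arm. Sidedness is a separate matter. I take the plan's 72 evaluable, 36 per arm, and test two-sided at 0.05.

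**2. What the statistic discards: a made-up table with 36 per arm.** Control is 12/12/12 (low/moderate/high).

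- Exercise A = 6/12/18. Column totals are 18, 24, 30 and expected counts 9, 12, 15. X² = (9 + 9)/9 + 0 + (9 + 9)/15 = 2 + 1.2 = 3.2; p = exp(−3.2/2) = 0.20; V = √(3.2/72) = 0.21.
- Exercise B = 6/18/12. The same terms arise in other columns, so X² = 3.2 and V = 0.21 again. Swapping the two arms changes nothing either.
- The linear trend statistic with scores 0, 1, 2 separates them. For A: 6²/[36·36/(72·71) × 46.0] = 36/11.66 = 3.09, p = 0.08. For B: 3²/[0.2535 × 41.5] = 9/10.52 = 0.86, p = 0.36.

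**3. Power.** None of these inputs is in the article; all are assumptions:

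- Class shares without effect: 33/33/33, 50/34/16, 31/53/16 or 40/40/20%.
- Latent normal activity score, shifted in the exercise arm by 0.4, 0.6 or 0.8 SD. The 0.6 borrows the size of the LVEF effect and is only a middle value.
- Latent correlation between baseline and follow-up: 0, 0.3, 0.5 or 0.7.

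Tests compared, with 20,000 simulated trials per setting (Monte Carlo error at most √(0.25/20,000) = 0.35 points per power figure):

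- Pearson: Σ(O − E)²/E on 2 df.
- Trend (order only): (N − 1)r² on 1 df.
- Stratified mean-score (order and baseline): [Σₛ Σ g(y − ȳₛ)]² / Σₛ {n₁ₛn₀ₛ/[Nₛ(Nₛ − 1)] · Σ(y − ȳₛ)²} on 1 df, with s the baseline class and g the arm.

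Ranges below are over the four class splits. Gains are in percentage points over Pearson.

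| Shift | Pearson power | Trend power | Stratified gain, corr. 0 | 0.3 | 0.5 | 0.7 |
|---|---|---|---|---|---|---|
| 0.4 SD | 24–25% | 31–33% | 6.1–7.0 | 7.7–8.7 | 11.5–11.9 | 17.9–19.4 |
| 0.6 SD | 49–52% | 60–62% | 9.1–10.2 | 11.6–12.2 | 16.6–17.4 | 26.2–27.1 |
| 0.8 SD | 74–78% | 83–86% | 6.6–8.1 | 9.0–9.9 | 12.3–13.3 | 17.5–19.5 |

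With no shift, all three tests reject in 4.7 to 5.4% of trials.

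**4. Splitting the gain.** The trend test alone gains 6.9 to 11.6 points. At correlation 0, where baseline carries no information, the stratified test gains 6.1 to 10.2. Order is therefore worth roughly 6 to 12 points; anything beyond that comes from the baseline class and depends on the assumed correlation. A proportional-odds likelihood-ratio test with baseline class, run on fewer trials (400 per setting), gave similar power.

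**The case against.** The strongest reply is that the activity outcome already has the better analysis. MET-minutes and sitting time are continuous, so they are "adjusted for the effect of the baseline values (covariate"). A reader might infer that the hypothesis of increased activity stands or falls with the chi-squared test. The article does not support that: the class is a coarser summary of a measure whose other forms use baseline, size and direction. This stands, and it confines the point to the class.

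Second, the chi-squared sentence names no outcome, arm contrast or time point, and could serve for education, clinical history or other tabulated data. This stands in part. Applying it to the class is an inference, but the natural one: descriptive frequencies are dealt with earlier in the section, the sentence follows the outcome models, and it carries effect-size cutoffs parallel to those for partial eta-squared. If it is meant for other tables only, the class has no stated test, and the same edit settles it.

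Third, frequencies will be reported, so the direction of any shift will be visible. That is true; only the planned effect size lacks a sign.

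Fourth, the power figures rest on assumed inputs, and a uniform latent shift favours tests that use order. That also stands, so the loss can only be given as a range.

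Finally, ordinal modelling of a secondary questionnaire category might be left to an analysis plan. But a method is stated here, and the comment concerns that choice, not missing detail.

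**Conclusion.** The point holds as a minor one. If chi-squared with Cramer's V is the between-arm analysis of the activity class, it discards the order of the levels and a baseline class that the trial collects, unlike the plan's own rule for continuous outcomes. The loss is about 6 to 27 points of power at 36 per arm, for assumed latent shifts of 0.4 to 0.8 SD and baseline correlations of 0 to 0.7; about 6 to 12 of these come from order alone. No single figure can be attributed to the plan, because it gives no class shares, effect or correlation for activity.

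A reader might also infer that the planned test is biased or invalid. It is not: type I error stays at about 5%. No primary outcome is touched, and the trial is not sized on activity.

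**What to change.** In Statistical analyses, add one sentence for the activity class at t2 and t3: a proportional-odds (ordinal logistic) model with arm and baseline class, reporting the odds ratio with its 95% confidence interval. Alternatively, specify a Cochran-Mantel-Haenszel row-mean-score test stratified by baseline class. Keep chi-squared and Cramer's V for nominal variables and descriptive tables.

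This needs no new data, visits or participants, and the ordinal model is available in the named software. The small cost is the proportional-odds assumption, which the stratified test avoids, although that test does not itself supply an odds ratio.

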### Blinding

This study will involve the prescription of exercise sessions. To carry out a rigorous exercise prescription and to ensure adequate follow up of each patient, participants, the physical trainer (PA), the medical oncologist (AJ), and the nurse oncologist (ALA) will not be blinded to group assignment. Due to the lack of resources, only the evaluators acquiring the echocardiographic outcomes (resting LVEF and LV global longitudinal strain), circulating NT-proBNP levels, cardiorespiratory fitness, and recovery HR data, will be blinded to the group assignment.

### Limitations

There are some limitations to this study, which should be noted. First, we will only include patients followed at CHVNG/E. Second, due to the impossibility of blinding patients and some of the researchers to study group assignment, the open design of this study may influence the assessment retention rate of participants allocated to the control group. Third, we will stratify our sample based on age (under/over 50 years) and use of trastuzumab (yes/no). However, there are other risk factors associated with ARC, including total cumulative anthracycline dose, pre-existing cardiac disease, and treatment with mediastinal radiation, that should also be considered [19]. Although these hinderances should be acknowledged, we believe the findings from the present study will provide important data, which will be of relevance to the contemporary literature on this subject.

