## Background

Over the last three decades the epidemiology of breast cancer (BC) has been marked by the clear increase in survival rates [1]. The accessibility of screening and the discovery of new therapeutic options are among some relevant factors related to the improved management of cancer. However, despite their undeniable clinical importance, anti-cancer treatments are also associated with frequent induction of side effects. Among those, cardiotoxicity emerges as a major challenge, limiting treatment options [2] and contributing to morbidity and mortality in this patient population [3–5].

In the BC setting, cardiotoxicity is typically associated with exposure to traditional cytotoxic therapies and particularly with the use of anthracyclines [6]. Anthracyclines are important and effective chemotherapeutic agents, frequently administered in curative and palliative regimens for BC, although their clinical use is limited by cardiac dysfunction, usually seen as cardiotoxicity [7]. The American Society of Echocardiography and European Association of Cardiovascular Imaging define cardiotoxicity as a decrease in left ventricular ejection fraction (LVEF) of > 10% to a value of < 53% [8]. However, it has been proposed that anthracycline-related cardiotoxicity (ARC) is a continuous [9] and dose-dependent phenomenon [10] that starts with acute myocardial damage [11], which can be detected by elevation of circulating cardiac biomarkers [12] and by impairment of left ventricular (LV) longitudinal strain [13], in turn preceding the commonly reported progressive decline in LVEF [9]. ARC may ultimately lead to overt heart failure, particularly when underestimated, not prevented or insufficiently prevented, or untreated, [9].

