### Randomization

After confirmation of eligibility and baseline assessments (t0), patients will be randomized using Internet software (www.sealedenvelope.com), in a 1:1 ratio to the supervised exercise group (intervention group) or the usual care group (control group), using a permutated block design with random block sizes (4, 6, 8) with stratification by two dichotomous variables, which are known risk factors for ARC:Age (< 50 years or older)Receiving anti human epidermal growth factor receptor 2 (anti-HER2) therapy (yes/no)

This process will be performed by an external individual who is blinded to the study and who will place the sequence in a numbered, opaque, sealed envelope. The allocation of participants will then be reported to an oncologist (AJ) who will subsequently inform the patients about the assignment group.

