### Demographic, anthropometric, and clinical data

Demographic, anthropometric, and clinical data will be recorded during the enrolment process (**−**t_0_). Demographic data include age, sex, and education. Anthropometric data include weight, height, and body mass index. Clinical data include disease, treatment information, past medical history, and current medication. These data will be extracted from the patients’ electronic medical files by two study coordinators (ALA, AJ) not blinded to the patient assignment group.

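### Planned anthracycline dose is left out of both the stratification and the ANCOVA models, which may cost a little precision; the size cannot be derived from the article

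*Protocol article*

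**What the plan says.** The Background of the protocol article calls anthracycline-related cardiotoxicity a "dose-dependent phenomenon [10] that starts with acute myocardial damage". The Limitations section returns to the subject: after naming the two stratification factors, it states that "there are other risk factors associated with ARC, including total cumulative anthracycline dose", and adds that such factors deserve consideration.

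The design and analysis sections do not use dose:

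- **Randomization.** Allocation is made "with stratification by two dichotomous variables, which are known risk factors for ARC": age (under 50 or older) and anti-HER2 therapy (yes or no).
- **Statistical analyses.** The one-way ANCOVA is "adjusted for the effect of the baseline values (covariate", and the repeated-measures ANCOVA is given that same single covariate.
- **Eligibility (Table 1).** Women must be scheduled for anthracycline-containing chemotherapy for stage IA to IIIC disease. The table fixes no regimen or dose, so planned dose may vary between participants.

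On timing, "Demographic, anthropometric, and clinical data will be recorded during the enrolment process", and "Clinical data include disease, treatment information, past medical history, and current medication". Allocation comes later: "After confirmation of eligibility and baseline assessments (t0), patients will be randomized".

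**The concern.** A covariate that is known before randomization and predicts the outcome can be adjusted for without compromising the randomized comparison. Doing so removes its share of the residual variance and corrects the estimate for whatever imbalance chance has produced. The article itself points to dose as a factor of this kind, yet treats it only as a limitation of the stratification. A factor that was not stratified on can still enter the model, and in a trial of 90 women that is the usual remedy.

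The Statistical analyses section names the covariate set for both models. The point therefore concerns what the article fixes, not detail left to a fuller document. At stake are the standard errors for NT-proBNP, longitudinal strain and LVEF, and how the result would be read if the arms happened to differ in planned dose.

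**Working it through.** **Inputs from the article (Sample size calculation).** Standardized effect 0.6 for LVEF, 80% power, significance level 0.05 with sidedness not stated, two-sample t test, 72 evaluable, 20% dropout, 90 randomized.

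**Inputs not in the article (assumed).** The share R² of residual outcome variance, beyond the baseline value, explained by planned dose; the split between regimens; the size of the dose effect.

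**1. The plan's own figure.** Exact t-test calculation at d = 0.6 and 80% power:

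- One-sided 0.05: 35.04, rounded up to 36 per arm, so 72 in total. This matches the article.
- Two-sided 0.05: 44.59, rounded up to 45 per arm, so 90 evaluable.
- Dropout: 72 / (1 − 0.20) = 90. This matches.

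At 36 per arm, power is 70.9% two-sided and 80.9% one-sided. The gap between 70.9% and 80% is a matter of sidedness in the sample size and is not caused by leaving dose out.

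**2. Gain from adjusting for planned dose.** Adjustment multiplies the residual SD by √(1 − R²), so the effective d is 0.6 / √(1 − R²). At 36 per arm, two-sided 0.05:

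| R² (assumed) | Effective d | Fall in standard error | Power |
|---|---|---|---|
| 0 | 0.600 | 0 | 70.9% |
| 0.01 | 0.603 | 0.5% | 71.3% |
| 0.04 | 0.612 | 2.0% | 72.7% |
| 0.05 | 0.616 | 2.5% | 73.1% |
| 0.10 | 0.632 | 5.1% | 75.4% |

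**3. Chance imbalance.** Assume two regimen classes split 50/50.

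- SD of the between-arm difference in the higher-dose share: √(0.5 × 0.5 × 2/36) = 0.118.
- P(|difference| > 0.15), normal approximation: 0.15 / 0.118 = 1.27, so about 20%.
- With an assumed dose effect of 0.5 SD, a difference of 0.15 shifts the estimate by 0.15 × 0.5 = 0.075 SD.
- Standard error of the group difference at 36 per arm: √(2/36) = 0.236 SD. The shift is 0.075 / 0.236 = 0.32 of a standard error, and 0.075 / 0.6 = one eighth of the design effect.

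**4. Consistency of the assumptions.** A 50/50 split with a 0.5 SD dose effect implies R² = 0.25 × 0.5² = 0.0625. Power is then 73.7%, a gain of 2.8 points. Reaching about 80% would need R² = 0.20, which with the same split means a dose effect of √(0.20/0.25) = 0.89 SD, larger than the 0.6 SD the trial is designed to detect.

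**The case against.** The strongest defence is that nothing here is invalid. Baseline-adjusted ANCOVA in a 1:1 randomized trial is unbiased in expectation and holds its type I error, and its standard error already allows for chance imbalance in unmodelled factors. That stands, and it confines the point to efficiency and conditional imbalance.

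A reader might infer that a chance dose imbalance would mimic or hide a cardioprotective effect. The article does not support that: under the illustrative assumptions, an imbalance exceeded in about one trial in five starts at a shift of about a third of a standard error. A reader might also infer that adjustment would restore 80% power. That needs a dose effect larger than the design effect, for which the article gives no basis.

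Two further objections are partly right.

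- The article speaks of total cumulative dose and never names planned dose. Cumulative dose as received accrues after randomization, so leaving it out of the model is correct. Only a dose or regimen fixed before allocation qualifies.
- That planned dose is captured is an inference from the general term for treatment data in the enrolment section. It needs confirming.

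The Limitations section does disclose the gap, but only for the stratification; the model remains open to change. It is also fair to say that other factors are omitted. The two stratification factors are absent from the model as well, and have at least as strong a claim to be covariates.

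**Conclusion.** The point holds as a low-severity suggestion. The article identifies dose as a determinant of the toxicity under study, then fixes a stratification and two models that do not use it. The consequence is a possible loss of precision and no adjustment for chance imbalance in planned dose. It is not bias and does not inflate the false-positive rate.

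The size cannot be derived from the article. If planned dose explains 5% to 10% of the variance left after baseline adjustment, the gain is about 2 to 4.5 power points at 36 per arm (two-sided 0.05, d = 0.6). At 4% or less it is under 2 points, and if regimens at this single centre are nearly uniform it is close to nothing. These figures rest on assumed R² values and on a two-sided test, which the article does not specify.

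**What to change.** First, confirm that the treatment information taken at enrolment includes the planned regimen or planned cumulative anthracycline dose, and that it is recorded before allocation. If it varies between patients, prespecify it as one additional covariate, alongside the baseline value, in the ANCOVA and the repeated-measures model for NT-proBNP, longitudinal strain and LVEF. A two-level regimen class would serve, as would a linear dose term on a common scale. Do not adjust for delivered dose, which accrues after randomization and may be affected by the arm.

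The cost is about one degree of freedom, plus the work of agreeing a common dose scale if agents differ; more than two regimen classes would cost more. If planned dose turns out to be nearly constant, no change is needed.
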